### The study will be undertaken in two sub-counties, and census enumeration areas will be randomized to either intervention or control. Registered drug shops located in intervention areas will receive training in the use of rapid diagnostic test for malaria (RDTs) and supplied with RDTs by the research team, and trained to only recommend antimalarial treatment with Coartem® after a positive test result. In the control areas, registered drug shops will continue to dispense antimalarial treatment based on presumptive diagnosis (current practice).

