***Methods***

*Diagnosis and treatment procedures*

Private providers will be trained on how to recognize and distinguish uncomplicated & severe malaria, supplying unit-dose packaged Coartem® to customers with uncomplicated malaria, and administration of rectal artesunate pre-referral treatment and referral for children with severe and complicated malaria. Rectal artesunate will be provided free of charge for children with severe malaria who cannot take oral medication.Shops will be provided with low literacy visual aids to help explain the symptoms, diagnosis, correct treatment of malaria and danger signs. The shopkeepers will explain the pictorial instructions to customers, as well as give instructions on dosing and how to give the drug to the patient.

Private providers in the intervention areas will be trained in use and interpretation of the rapid diagnostic test. Shops will be supplied with RDTs and a placard identifying them as an approved provider of malaria diagnostic tests. Private providers will be allowed to sell the test, at a price determined by pre-intervention willingness-to-pay studies. The age and sex of patient, onset of symptoms and promptness of treatment-seeking, diagnosis (including RDT result, where appropriate), tablets supplied and outcome of treatment will be recorded by dispensers. Drug sellers will also be trained in the preparation of thick blood films for malaria, and a research blood slide will be prepared from all patients being treated with an antimalarial drug (irrespective of use of RDT) for later validation of diagnosis and treatment by microscopy. All drug sellers will be trained on good laboratory practices, proper disposal of sharps etc. Sharps containers will be provided, and collected regularly for correct disposal at the health facility by the research team.

Consent will be obtained from drug shop owners to participate in the trial, and for randomization of shops to receive RDTs.

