Patients are free to choose which shops they use, and will be able to choose between outlets that offer diagnostic testing and those that do not, as this service will be openly advertised. Patients seeking treatment for uncomplicated malaria (or fever) from a registered drug shop in the intervention areas will be offered a RDT prior to drug purchase. Verbal consent will be sought from patients accepting the test, to also prepare a blood film from the fingerprick blood sample for the purposes of the research. Patients who decline an RDT test (and patients seeking treatment at registered drug shops in non-intervention areas) will receive presumptive treatment, as per current practice. This outcome (no test) will be recorded and whether an antimalarial was purchased or not.

Community sensitization on the need for treatment of febrile illness within 24 hrs after onset of illness will also be carried out. Sensitization meetings will also aim to increase awareness of ACTs within the community, the need for better diagnosis, and the importance of adherence to treatment.

*Referral mechanism of severe malaria and non-malarial fevers*

Severe malaria: Children with danger signs consistent with suspected severe malaria (WHO definition 2000) will be given pre-referral treatment using a rectal artesunate suppository and referred immediately to the nearest health unit for further treatment. Patients will be referred using an emergency referral form, including details of symptoms and the use of pre-referral treatment. Shops will keep a dated register for referrals and copy of the referral form with personal identifiers (also at health units).

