Non-malarial fevers: By law, registered class C drug shops are not permitted to stock antibiotics or other “prescription only” medicines. Commercial drug sellers will therefore also be trained to examine and refer febrile patients with fever (axillary temperature >37.0OC and a negative RDT (i.e. non-malaria) to the nearest health facility for examination and treatment by a fully qualified health worker, where appropriate. Any patient with danger signs and/or a temperature >38.5OC and a negative RDT should be referred to the nearest health unit as an urgent case. This additional temperature criterion is based on the WHO definition of hyperthermia and is intended to help ensure that those with severe bacterial infections are seen at a health unit. These patients will also be referred using the emergency referral form, which includes details of symptoms and the use of prior treatment. Shops will keep a dated register for referrals and copy of the referral form with personal identifiers (also at health units).

Shopkeepers will be trained to advise RDT negative patients with fever (axillary temperature ≥ 37.0OC) or other symptoms to seek treatment at the nearest health facility for further evaluation by a fully qualified health worker. A standard referral form will be provided to the patient for this purpose. Where no other symptoms are present, the patient will be advised on tepid sponging, but to return for further assessment at the drug shop or a health facility should the symptoms persist or worsen.

To minimise the risk of inadvertent exposure to ACTs during pregnancy, drug sellers will be trained to administer and RDT test, and to refer RDT-positive pregnant women (or women that suspect they may be pregnant) to a health facility for examination by a midwife prior to antimalarial treatment.

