**ETHICAL ISSUES**

**Discuss ethical aspects of the proposal.**

*Treatment & referral:*

Patients seeking treatment for fever from a registered drug shop in the intervention areas will be offered a RDT prior to drug purchase. Patients declining a test (and patients seeking treatment at registered drug shops in non-intervention areas) will receive presumptive treatment, in accordance with national guidelines for home-management of malaria (current practice).

Shopkeepers will be trained in taking a fingerprick blood sample, and sterile precautions. Sharps containers will be provided, and collected regularly for correct disposal at the health facility by the research team.

Shopkeepers will be trained on how to recognize and distinguish uncomplicated & severe malaria, supplying unit-dose packaged Coartem® for patients with uncomplicated malaria and the administration of rectal artesunate pre-referral treatment to children with severe and complicated malaria. Cases of severe malaria will be referred immediately to the nearest health unit. In case of a febrile patient with a negative RDT (i.e. non-malaria), those with danger signs and/or axillary temperature >38.5 will also be referred to the nearest health unit. This additional temperature criterion is based on the WHO definition of hyperthermia and is intended to help ensure that patients with severe bacterial infections are seen at a health unit.

To minimise the risk of inadvertent exposure to ACTs during pregnancy, drug sellers will be trained to administer and RDT test, and to refer RDT-positive pregnant women (or women that suspect they may be pregnant) to a health facility for examination by a midwife prior to antimalarial treatment.

*Informed consent:*

Consent will be obtained from drug shop owners to participate in the trial, for randomization of shops to receive RDTs, to keep records on diagnosis and drug sales, and to make these available to the research team. Meetings will be held with the communities in the study areas to describe the purpose of the study, the procedures to be followed, and the risks and benefits of participation.

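### The pregnancy safeguard is most naturally read as triggered by a positive RDT, so it does not clearly cover untested women, who go to presumptive treatment with no stated pregnancy exception

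*Protocol*

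**What the plan says.** Pregnancy is addressed in two places, in the same words: section (c), Referral mechanism of severe malaria and non-malarial fevers, and Ethical issues, Treatment & referral. The purpose and first step are: "To minimise the risk of inadvertent exposure to ACTs during pregnancy, drug sellers will be trained to administer and RDT test". The second step is to "refer RDT-positive pregnant women (or women that suspect they may be pregnant) to a health facility for examination by a midwife", before antimalarial treatment.

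Four other statements decide whom this reaches:

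- **RDT training** (Diagnosis and treatment procedures): "Private providers in the intervention areas will be trained in use and interpretation of the rapid diagnostic test". Study design likewise supplies RDTs to shops in intervention areas, and control shops carry on with presumptive diagnosis.
- **Untested patients** (Methods): "Patients who decline an RDT test (and patients seeking treatment at registered drug shops in non-intervention areas) will receive presumptive treatment". Ethical issues repeats this: "Patients declining a test (and patients seeking treatment at registered drug shops in non-intervention areas) will receive presumptive treatment", and adds that such treatment follows national home-management guidelines.
- **Drug supply** (Diagnosis and treatment procedures): private providers are trained in "supplying unit-dose packaged Coartem® to customers with uncomplicated malaria". This sentence names no arm. The paragraph on RDTs that follows it does.
- **Dispenser record** (same subsection): "The age and sex of patient, onset of symptoms and promptness of treatment-seeking, diagnosis (including RDT result, where appropriate), tablets supplied" and treatment outcome. Pregnancy is not on the list.

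**The concern.** The protocol sets itself a safety aim, avoiding inadvertent ACT exposure in pregnancy, and ties it to a test that many clients will not have. No control-shop client is tested by the shop, and some intervention-shop clients will refuse. These clients may be sold an antimalarial without confirmed malaria, so for them a pregnancy check matters at least as much as for tested women. A seller who follows the text has an instruction to treat presumptively and no clear instruction to ask about pregnancy first.

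This is a question of participant safety in the trial procedures. It does not affect the validity of the statistical comparison.

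**Working it through.** The protocol gives no figure to reproduce on this point. The check sets the passages side by side.

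**Who is covered, taking the positive RDT as the trigger**

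| Pregnant or possibly pregnant client | What the protocol directs | Covered? |
|---|---|---|
| Intervention shop, RDT-positive | Referral to a midwife before antimalarial treatment | Yes |
| Intervention shop, RDT-negative | Sellers are trained to recommend Coartem only after a positive result | Indirectly |
| Intervention shop, test declined | Presumptive treatment, no exception stated | Not clearly |
| Control shop | No RDT; presumptive treatment, no exception stated | Not clearly |

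**Does the research blood slide fill the gap?** No. It is read later by microscopy to validate diagnosis and treatment, so the seller has no result at the point of sale.

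**Two readings of the parenthesis about suspected pregnancy**

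1. *RDT-positive governs both groups.* The sentence opens with giving the test, so this is the more natural reading. Untested women then fall outside the rule.
2. *The parenthesis stands free of the test result.* Untested women who suspect pregnancy would then be referred, and a sensible seller would treat known pregnancy the same way. But this reading conflicts with the presumptive-treatment sentences in Methods and in Ethical issues, neither of which has an exception.

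On either reading the text needs one clarifying sentence.

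**Does the unrestricted term for drug sellers extend the rule to control shops?** If it does, control sellers would have to test women with RDTs they are neither trained on nor supplied with. That would contradict Study design. So it does not resolve the point.

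**Size.** Sample size requirements plans at least 620 adults per arm, and none of the control-arm adults would have a shop RDT. Going from there to a number of exposed women needs three further quantities: the share who are women, the share of those who are pregnant, and the share of untested pregnant women who buy an ACT. The document gives none of them. Its purchase figures (fewer than 40% of adults buying any antimalarial; 50% buying an ACT as a planning value) are not specific to pregnant women. No count is derived here.

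**The case against.** **National guidelines may already cover this.** Ethical issues places presumptive treatment under them. If they restrict ACT use in pregnancy, the protocol takes in that restriction by reference. This stands as a limit on the claim, since exposure cannot be shown from the document. It does not remove the point: the investigators wrote a pregnancy rule of their own, and its reach should be clear.

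**Operational detail may sit in training materials.** This is a page-limited proposal, and sellers may in practice be told to ask every woman. That is possible. But the protocol does fix a trigger, and it fixes it too narrowly.

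**Control shops should stay at current practice.** A screening question and a no-sale referral touch antimalarial sales, which the trial measures. This is a real trade-off. However, the Coartem and severe-malaria training has no arm limit either, so control shops are not wholly untouched, and the RDT contrast would remain.

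**Records already exist.** The protocol keeps a dated referral register with copies of forms for severe cases and urgent RDT-negative cases, and exit interviews ask about referral. This is a fair point: extending that register is enough, and no separate record system is needed. A register of referrals will still not show pregnant women who were sold a drug without referral.

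**A stronger reading concerns the endpoint.** Under the composite definition, a slide-positive pregnant woman who is correctly referred without a drug counts as inappropriately treated. A reader might infer that the primary endpoint needs changing. The documents do not support that. Under the current rule the effect runs against the intervention, and it is limited to this small group. Redefining the endpoint would also make it depend on referrals recorded by sellers who know their arm, where it now rests on the slide and the drug given or sold.

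**Conclusion.** The point holds as a gap in the wording of a safety procedure. As most naturally read, the pregnancy referral requires a positive RDT. It therefore does not clearly reach control-shop clients or intervention-shop clients who decline the test, although sellers are trained without arm limit to supply Coartem.

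This rests on two judgements: that RDT-positive governs the parenthesis, and that the Coartem training applies in both arms because no arm is named. A reader might infer that the trial will expose untested pregnant women to ACTs, or might attach a number to that. Neither follows. The guidelines are not shown, presumptive treatment need not be an ACT, and the shares needed for a count are absent. Exposure is possible rather than proven.

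This is a cheap improvement worth making.

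**What to change.** 1. In the referral subsection and in Ethical issues, state: in both arms, before selling an antimalarial to a woman who could be pregnant and who is RDT-positive or untested, the seller asks about pregnancy. Any woman who is or may be pregnant is sent to a health facility, where a midwife sees her before antimalarial treatment is given.
2. In the presumptive-treatment sentences of Methods and Ethical issues, add: except women who are or may be pregnant, who are referred.
3. Log these referrals in the existing referral register.
4. Leave the definition of appropriate treatment unchanged in Evaluation and in Sample size requirements.

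**Cost.** One screening question is added to training that is already planned, with a few lines of protocol text and one more type of entry in the register. A standard referral form is already provided for, and the study undertakes to keep public facilities stocked. There are two downsides. Control shops depart slightly from current practice, which may shift a few control-arm sales. Referred women must also travel, a burden the protocol already accepts for RDT-positive pregnant women.

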***Evaluation***

*Appropriateness of treatment and/or referral*

Prescription patterns and drug sales in private shops and clinics will be measured through the use of exit interviews, drug sales records and mystery shopper visits. Drug sales records will be adapted to include data on RDT results. Semi-structured exit interviews will be used to ascertain whether diagnostic testing was offered, was accepted by the patient, and type and quantity of drugs sold. Exit interviews will also investigate the patient’s perception of diagnostic testing and their knowledge and understanding of the test result, treatment advice and/or referral. In non-intervention areas, a finger-prick blood sample will be taken to prepare a research blood film to ascertain by microscopy whether the fever was due to malaria. A random sample of patients will also be followed at home after several days to ascertain adherence to treatment (see section below), outcome of the illness and total household expenditure on treatment. Patients will be recruited on exit from the drug outlet and individual informed consent will be sought from patients (parents or guardians, in the case of minors) to participate in an exit interview and any subsequent household visits.

The appropriateness of treatment provided will be evaluated as the proportion of correctly treated malaria cases, based on the “gold standard” of the research blood slide read by an experienced research technician. Appropriate treatment of fever is a composite definition including both a) those who a slide-positive who are given a 1st-line antimalarial and b) those who are slide-negative who are not given a 1st-line antimalarial. Over-prescription will also be assessed as the proportion of children who are not parasite positive who receive inappropriate ACT treatment.

The perceptions and acceptability of the use of RDT prior to malaria treatment will also be evaluated among both users and providers of treatment services through a series of focus group discussions held with commercial drug sellers and local community members. The cost of diagnostic testing in commercial outlets may well influence acceptability and will be an important parameter to investigate. The perceived trade-off between the risk of paying for diagnosis compared to the cost of paying for inappropriate and thus ineffective medicines in the eyes of the local community will be critical to the acceptability of diagnostic testing, and may also change in light of actual experience over time. Willingness to pay and other factors affecting acceptability will be investigated through exit interviews, in-depth interviews with household heads and focus group discussions. Interviews and group discussions will be conducted before and after the introduction of diagnostic testing. Informed consent will be sought from all informants prior to undertaking any interviews (focus group discussions, exit interviews, household surveys, etc.).

Household surveys will be undertaken to collect information on treatment–seeking behaviour and associated costs, primary access point for ACTs, and consumer preferences. Data on the socioeconomic profile of households will also be obtained. The geolocation of households and local treatment providers will be mapped using handheld global positioning system (GPS). The study will be conducted over a period of 24 months.

*Adherence with treatment*

Knowledge of patient adherence to the course of medication is critical in evaluating the effectiveness and appropriate deployment of ACTs. Incomplete adherence may help accelerate the development of drug resistance. Poor adherence to medication has been previously described for chloroquine and other drugs, and is likely to occur also for ACTs. Caretakers may forget to give the dose on some days or may stop medication if they perceive that patient is cured after one or two doses. In particular however, the higher cost of ACTs may cause families stop medication after one or two doses to save tablets for later use, rather than complete the full course of treatment, or patients may only purchase a few tablets (partial dose) in order to save money.

Adherence to medication will be examined in a random sample of drug store clients recruited on exit from the drug outlet. Patients will be followed-up in their homes on day 4 to check on adherence to medication. The blister pack will be examined for any remaining tablets to assess compliance, using the following definition:

- *Total:* verbal confirmation of completion of all doses in presence of an empty blister pack and a correct description of how the dose was taken.
- *Probable:* confirmation of completion of all doses in the absence of a blister pack and a correct description of how the dose was taken.
- *Non-compliance*: presence of tablets on the blister pack on Day 4 and or inability to explain how the doses were supposed to be taken

In addition, in a randomly-selected sub-sample of 600 patients, a 100µl finger-prick blood sample on day 4 will be pipetted onto filter paper to measure drug levels by HPLC method to confirm adherence. As the presence of artemether derivatives in the bloodstream is shortlived and thus difficult to measure, adherence will be based on levels of lumefantrine alone. Furthermore as lumefantrine is taken on every day of treatment (whereas artemether is only given on day one) this will provide a measure of complete adherence up to and including day three.

*Measuring the economic impact of intervention*

Cost and cost-effectiveness: To determine relative cost-effectiveness requires information on resource use (costs) as well as effectiveness of each intervention arm. Analyses will be undertaken form a societal perspective and costs will include a) those related to deployment of the intervention and borne by the health service, and b) those incurred to the household when seeking treatment for fever, including the direct costs of transport, diagnosis and drugs, and opportunity costs of lost time and production. Both recurrent and capital costs to the provider of training staff and delivering the intervention will be estimated in both scenarios of private and public providers. Resource savings to providers and households will also be assessed. Household costs will be captured through a standardised questionnaire administered during periodic household surveys to capture data on treatments sought for febrile children in the 14 days prior to the survey, and will include a minimum of 500 questionnaires. Household surveys will be carried out during the malaria transmission season, and will be repeated at least twice, pre- and post-intervention. If resources allow, more frequent surveys will be carried out to examine seasonal variations in expenditure. The unit costs to the provider of malaria treatment will be estimated at a sample of health facilities and CDDs using a combination of standard step-down costing methodology and micro-costing.

Data on the incremental cost-effectiveness of adding RDT to presumptive treatment will be generated through a pairwise comparison of groups receiving ACT treatment after a positive RDT with presumptive treatment only. Net cost-effectiveness will be calculated by deducting resources saved from the total intervention cost per case of inappropriate treatment averted.

Cost-effectiveness will vary according to levels of community uptake and compliance under different implementation conditions. Furthermore, many of the parameters included in cost-effectiveness calculations are uncertain and variable (e.g. probability of death, unit costs of drugs, unit costs of diagnostic tests, and other inputs). Sensitivity analysis will therefore be conducted on the values of key parameters, in order to explore varying scenarios and to generate a range of potential cost-effectiveness ratios.

Coverage & Equity: Coverage of prompt effective treatment within 24 hours of onset of fever will be measured through household surveys in a random sample of communities, using a 14-day recall of fever cases in the household to obtain data on treatment-seeking behaviour. The equity of access to enhanced diagnosis in the treatment of malaria in young children will be assessed in terms of total levels of utilization, as well as proportional utilization of the public and private sector, across socio-economic groups. Socio-economic status will be examined in terms of wealth, based on ownership of household and agricultural assets. Utilization will also be compared between households differing in their educational background; specific knowledge of malaria and its treatment; and distance from nearest treatment provider. The equity of provision of treatment with/without improved diagnosis will be also compared according to levels of utilization of public provider (government health units) and private providers (pharmacies and drug shops).

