### *Secondary endpoints*

- Proportion of patients receiving prompt effective treatment from a commercial drug outlet: % of patients diagnosed with malaria who receive appropriate2 ACT treatment within 24 hours of onset of malaria.
- Acceptability of RDTs: % of patients offered a diagnostic test, % of ACT sales preceded by a test
- Perceptions of ACTs and other antimalarial drugs (amongst community; drug sellers; health staff)
- Perceptions and acceptability of malaria diagnosis using RDTs (amongst community; drug sellers; health staff)
- Willingness to offer and perform RDTs to malaria patients (among drug sellers, health workers)
- Patient adherence to prescription (complete dose taken by day 4)
- Referral: Appropriate treatment of RDT negative patients (lack of antimalarial sale and provision of referral); Timeliness and uptake of referral at a health unit by referred patients.
- Coverage of prompt effective treatment: % of patients with fever who received ACT treatment within 24 hours of onset of malaria, measured through household surveys. For comparison with the WHO/RBM indicator in national and international statistics, coverage in children <5 years will be reported separately from older children and adults.
- Source of treatment: % of patients attending health facility for treatment; % visiting a drug shop
- Equity of diagnosis: % of malaria patients receiving a diagnostic test for malaria, across socio-economic groups.
- Equity of treatment: % of patients, who are diagnosed with malaria, receiving treatment with an ACT, across socio-economic groups.

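### A single day-4 lumefantrine level is said to measure complete adherence to day three, but courses missing a middle day, the last day or the last dose overlap with full courses

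*Protocol*

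**What the plan says.** The Protocol, section (c), Evaluation, under the heading on adherence with treatment, has two layers. The first is a day-4 home visit to a random sample of drug-shop clients. The blister pack is inspected, the patient or caretaker is interviewed, and the course is classed as Total, Probable or Non-compliance.

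The second layer is added "in a randomly-selected sub-sample of 600 patients": a filter-paper blood sample on day 4, used "to measure drug levels by HPLC method to confirm adherence". The analyte is explained by "As the presence of artemether derivatives in the bloodstream is shortlived and thus difficult to measure", so that "adherence will be based on levels of lumefantrine alone". A further reason is given, "as lumefantrine is taken on every day of treatment (whereas artemether is only given on day one", and the conclusion drawn is that "this will provide a measure of complete adherence up to and including day three".

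The endpoint served is listed under Secondary endpoints: "Patient adherence to prescription (complete dose taken by day 4". The same adherence section names the failures it expects. Caretakers may forget doses on some days, patients may buy only part of a course, and cost may make "families stop medication after one or two doses to save tablets for later use".

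**The concern.** The endpoint asks whether the whole course was taken. The protocol says that a single later drug level answers this, on the ground that the drug is taken on each day. Daily intake shows only that each day contributes to the level. It does not let one number show that every contribution is present. If the drug is still measurable on day 4, the level is a sum over doses, and a missing term has to be distinguished from ordinary differences between patients in absorption, body size and time since the last dose.

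If a passing level is read as confirming completion, some incomplete courses are confirmed as complete. Reported adherence would then be biased upwards, and a true difference between arms could be diluted. The sentence asserts a property of the test, so it is not a detail that a later analysis plan could supply. A cut-off set later would fix the trade-off between the two errors but would not remove the overlap.

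**Working it through.** The protocol states no sensitivity, specificity or cut-off for the assay, so there is no figure to reproduce. The check asks how far the level falls for different missed doses, and how often the fall would be recognised.

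**Inputs.** From the protocol: one sample on day 4, and lumefantrine taken on each of three days. Assumed, because the protocol does not give them:
- equal amounts each day, first-order elimination, sample 24 h after the day-three intake;
- half-life h of 24 to 144 h;
- lognormal between-patient variation with CV of 40% to 80%;
- a cut-off that 95% of full courses pass;
- for the missed last dose only, six equal doses 12 h apart, sampled 24 h after the sixth. This is a modelling device and not a statement about the regimen.

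**Level relative to a full course (R).** Let r = 2^(−24/h). The full course gives r + r² + r³. Day three missed gives r² + r³, middle day missed gives r + r³, and day one only gives r³. For six doses let q = 2^(−12/h). The full course is then q² + … + q⁷, and with the last dose missed it is q³ + … + q⁷.

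**Detection.** P = Φ(−1.645 + ln(1/R)/σ), with σ = √ln(1 + CV²). This gives σ = 0.385, 0.555 and 0.703 for CVs of 40%, 60% and 80%.

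**Worked case, day three missed.** At h = 24 h, r = 0.5, so R = 0.375/0.875 = 0.429. With CV 40%, P = Φ(−1.645 + 0.847/0.385) = Φ(0.55) = 71%. At h = 144 h, r = 0.891, so R = 1.501/2.392 = 0.628. With CV 80%, P = Φ(−1.645 + 0.466/0.703) = Φ(−0.98) = 16%.

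| Course taken | R at 24 / 72 / 144 h | Detected: 24 h, CV 40% | 72 h, CV 60% | 144 h, CV 80% | Range over the grid |
|---|---|---|---|---|---|
| Day three missed | 0.43 / 0.59 / 0.63 | 71% | 25% | 16% | 16–71% |
| Middle day missed | 0.71 / 0.67 / 0.67 | 22% | 18% | 14% | 12–27% |
| Last of six doses missed | 0.67 / 0.78 / 0.81 | 28% | 11% | 9% | 9–28% |
| Day one only | 0.14 / 0.26 / 0.30 | about 100% | 78% | 53% | 53–100% |

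The grid is half-lives of 24, 48, 72, 96 and 144 h crossed with CVs of 40%, 60% and 80%.

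**Does a different half-life rescue the claim?** For a missed middle day, R = (1 + r²)/(1 + r + r²). This falls from 1 as r goes to 0 to 2/3 as r goes to 1. In this model the level therefore never drops below two thirds of the full-course value, whatever the half-life. A short half-life exposes a missed last day (R = 0.06 at 6 h) but hides a missed middle day (R = 0.94 at 6 h). Over a wider grid (half-life 6 to 120 h, CV 30% to 120%), the 95% cut-off passes 61% to 94% of middle-day-missed courses, 0% to 87% of last-day-missed courses and 0% to 63% of day-one-only courses.

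**Does a stricter cut-off rescue it?** With a cut-off that only 80% of full courses pass, 30% to 78% of middle-day-missed courses still pass, and one complete taker in five is failed.

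**The case against.** The strongest reply is that the assay is quantitative, is an addition to the pack check, and works well for the behaviour that most worries the protocol. Much of this stands.

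- **Early stopping is often visible.** A day-one-only course leaves 14% to 30% of the full-course level and is detected in 53% to 100% of cases. A reader might infer that the assay cannot tell full from partial courses, or that most incomplete courses would be confirmed as adherent. The documents do not support either: the answer depends on the half-life, variability, cut-off and pattern of omission, and the protocol fixes none of these.
- **The pack check remains.** In context, "adherence will be based on levels of lumefantrine alone" most naturally means lumefantrine rather than artemether as the analyte. It need not mean that the level replaces the classification. Inspecting the blister pack is itself an objective check, and tablets left on it already count as Non-compliance.
- **No any-detection rule is stated.** A reader might suppose that any measurable lumefantrine would count as adherent. The protocol says only that levels will be measured.
- **Cut-offs and timing fields may be in documents not shown.** Their absence is not the finding.
- **The artemether premise.** A reader might see a conflict between artemether on day one only and the product named in the design and treatment sections. Those sections do not give the daily content of the course, so the documents do not show a contradiction, and the point here does not depend on it.

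None of this defends the inference from daily intake to a measure of complete adherence.

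**Conclusion.** The claim attached to the day-4 level is too strong. A single level can support a conclusion about intake, and a very low level can show that a course was largely not taken, but a passing level does not establish that every dose was taken. The weakness is specific to late or intermittent omission: over the main grid, 29% to 84% of courses missing day three, 73% to 88% of those missing the middle day and 72% to 91% of those missing only the last dose would pass. These figures rest on assumed half-lives, CVs and a cut-off and are illustrative. That the level sums the residue of all doses, and that a missed middle day leaves at least two thirds of the full value under equal daily amounts, does not depend on the assumed half-life.

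The consequence is limited to one secondary endpoint and a supplementary sub-study. The primary endpoints and the sample size are not affected. Used as confirmation of completion, the assay would tend to overstate complete adherence.

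**What to change.** Replace the final sentence on the assay with a statement that the day-4 lumefantrine level is supportive evidence of intake and does not by itself establish completion. In addition:
- State explicitly that the Total, Probable and Non-compliance classification remains the adherence endpoint, and that lumefantrine alone refers to the choice of analyte.
- Record the time of the last reported dose and the time of sampling.
- Report lumefantrine as a continuous level by arm and by age or dose band, adjusted for hours since the last dose, with patients classed as Total as the in-trial reference distribution.
- Use the assay categorically only to flag undetectable or very low levels.

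The cost is protocol wording and two time fields on the day-4 form. No extra samples or patients are needed. The downside is a more modest claim for the 600-patient sub-study. The reference group also rests partly on self-report, so it is a comparison distribution and not a directly observed standard.
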